### **3.2.4. Survey organization**

Both the baseline and endline surveys will take place during home visits conducted by qualified interviewers, duly selected and trained for this specific study. They will be directly supervised and evaluated by experienced agents. The questionnaire will be administered confidentially, ideally over a period of 90 to 120 minutes, and will be followed by 10 to 15 minutes of anthropometric measuring conducted under standardized conditions. The questionnaires will be digital and loaded onto tablet PCs (via the Open Data Kit [ODK] system), except for the questionnaires regarding village characteristics and household composition.

Four interviewer-pathfinder duos will be charged with notifying and sensitizing the villages and households involved in the study. They will explain the study objectives, inform subjects of their next interviews, and obtain the necessary prior approval. These duos will also be in charge of completing the questionnaire concerning the village and will take a census of all members of households involved in the study to complete the household composition questionnaire. The duos will therefore pass from village to village a few days before the interviewers visit.

Approximately 30 interviewers will be recruited and trained on the questionnaires and anthropometric measurements. Five supervisors will be hired, each responsible for a team of six people. In order to guarantee the quality of the data, supervisors will initially accompany interviewers in person (thus making sure they are correctly administering the questionnaires, correctly entering collected data, etc.). A dedicated server will receive regular transmissions of data, so study directors can remotely monitor both the figures and work progress.

### **3.2.5. Data collection and indicators**

Data will be collected at different levels, namely, households, mothers, and children. The following is a list of the main components and key indicators to be gathered:

❖ **HOUSEHOLD LEVEL**

**Household composition and characteristics:** household size, head of household’s sex, revenue source, household members’ education levels, children’s schooling (past and present), children’s participation in household income generation, number of foster and/or adopted children in the household and reasons for their being there.

**Household socioeconomic level:** This will be evaluated by assessing housing quality and household assets. We are particularly interested in: the quality of building materials (roof, walls, floor), the presence of an electrical connection and running water, the presence or absence of a number of everyday household objects, productive assets, livestock, and agricultural land. A synthetic index representing households’ economic levels will be created using a factor analysis; this technique consists of weighting different categories of a number of variables which indirectly reflect household affluence. The resulting score is a dimensionless variable, interpreted for each household as an approximation of its level of wealth. The score could be used in analyses as a continuous variable, but after categorization into tertiles or quintiles, it may also be used to classify households by income level.

**Household food expenses**: These will be obtained through a 24-hour diet recall, either over a week or a month depending on whether food is purchased daily, weekly, or monthly. All of these expenses will be scaled to a monthly figure, totaled, and divided by the number of adult equivalents in the household. The number of adult equivalents is based on the value of individual energy needs with regard to age, sex, and level of physical activity, according to international values. The reference individual is a man between 30 and 59 years old, moderately physically active, who requires 2,450 Kcal daily. Thus, if an individual’s daily energy need is 1,225 Kcal (roughly equal to that of a nearly four-year-old girl), they are counted as 0.5 of an adult equivalent.

**Household non-food expenses:** These will be calculated based on the following items: lodging (rent, maintenance), cooking fuel source, electricity, water, health and education, hobbies, personal hygiene, clothing, shoes, vehicles, beauty care services, and communication. All of these expenses will be scaled to a monthly figure, which will then be weighted according to the household’s adult equivalent number as described above.

**Household food insecurity access scale (HFIAS):** The HFIAS scale permits a holistic look at households’ food insecurity, based on consequences and feelings stemming from recent experiences with food insecurity and strategies developed to deal with it. This instrument is inspired by the Radimer-Cornell scale, developed and employed in the United States within the framework of its federal food assistance programs, and has been adapted for use in developing countries following several tests and validation experiences. Scores are calculated based on responses to nine questions that address the various dimensions of food insecurity in order of increasing importance, according to current recommendations. Each response is marked between 0 (a “no” response) and 3 (1 to 3, depending on how frequently the household experiences the situation in question). The reference period comprises the prior month. The final score will thus range between 0 (indicating a food-secure household) and 27 (maximum food insecurity). Additionally, households’ experiences with the most severe consequences place them in one of four categories (food-secure and slightly, moderately, or severely food-insecure).

**Household economic shock:** Some households may experience economic shock during or just before the program that affects the family environment and, consequently, children. It is therefore invaluable to glean this information retrospectively in the context of this evaluation. If indeed a household experiences economic shock during the program, it may explain any possible lack of positive program impacts.

**Hygiene and sanitation:** Household hygiene can have a large impact on children’s health and nutritional status. We will employ spot checks to estimate the cleanliness of the property and its inhabitants, which have proved to be an efficient, non-intrusive, quick, and affordable approach. A short questionnaire on household sanitation (toilets, wastewater systems, and trash) will supplement this method.

❖ **PERTAINING TO MOTHERS**

**Mother’s characteristics:** This component consists of mothers’ civil statuses, education levels, and revenue sources.

**Schedule and child care:** Mothers’ schedules will be examined, as they can directly influence dietary practices and child care. The time mothers spend taking care of their children (meals, games, healthcare) will be observed with particular interest.

**Mother’s status, autonomy, and decision-making power:** This component will assess women’s household autonomy (particularly with regard to finances), the treatment they endure within the household (abuse, insults, anxieties, etc.), their involvement in sensitization meetings and social/community networks, and their decision-making power relative to issues of diet, health, education, family planning, and children’s rights within their households.

**Use of health services and attendance at informational sessions:** This component will take into account pregnancy history, household situations during the course of pregnancy (reduced work, improved diet, etc.), the number of pre- and post-natal consultations, birth setting and external help received, and mothers’ involvement in training sessions on children’s health, diet, and rights.

**Mother’s knowledge, attitudes, and practices (“CAP”):** The program aims to improve mothers’ knowledge bases in order to impact their dietary practices and their conduct relating to the caretaking, hygiene, nutrition, and rights of their children. After adjusting for certain variables such as education and socioeconomic levels, changes in the CAP between the baseline and endline surveys will be examined to evaluate the program’s impact pathways. The CAP questionnaires will be adapted to the content of the monthly information sessions planned in the project.

**DIetary diversity:** A dietary diversity score will be calculated for each mother following a qualitative recall of items consumed over the previous 24 hours. These scores will be determined by tallying the number of food groups consumed out of 12 total food group classifications. However, as there are currently no international recommendations for an optimal number of food groups or a “good dietary diversity” threshold for women of childbearing age, information will be collected from a larger number of groups and subgroups; thus, indicators can be constructed *a posteriori* according to recommendations adopted in the future (which should soon be implemented on an international level, hence during program implementation).

**Anthropometry:** Mothers’ height and weight will be measured in accordance with WHO recommendations. Along with body mass index, this raw data can be used to evaluate mothers’ nutritional statuses, which are known as a major factor in newborns’ nutritional statuses at delivery.

❖ **PERTAINING TO CHILDREN**

**Child’s health:** This component will gather information regarding possession of health records, children’s immunizations, growth charts, and children’s morbidity over the previous 15 days. Additionally, in cases of illness, mothers’ appetites and responses to said illnesses will be assessed during consultations at a health center (or elsewhere).

**Dietary practices:** Standard dietary practices indices for infants and young children, as recommended by the WHO, will be calculated following a qualitative recall of children’s feeding practices over the last 24 hours—for example, dietary diversity (number of food groups consumed out of seven total), frequency of ingestion (total number of meals and snacks consumed), consumption of foods of animal origin, consumption of iron-rich products, etc. Retrospective questions about breastfeeding will also be asked (initiation and cessation, exclusive breastfeeding), as well as questions about the introduction of complementary feeding and how the mother feeds her child (preparation of specially adapted meals, help with eating, encouraging consumption).

**Child welfare and rights:** The relevant MICS (Multiple Indicator Cluster Surveys) module will be used. Among other items, it includes questions about birth registration, child labor, schooling, child marriage, children’s education and discipline, and disabilities. It will be particularly important to observe whether attitudes and practices evolve with the program.

**Anthropometry:** Children’s height and weight will be measured in accordance with WHO recommendations in order to calculate height-for-age and weight-for-height nutritional indices, and will be expressed as *z*-scores using the WHO reference curves for growth from 2006.

❖ **PERTAINING TO SCHOOL-AGED SIBLINGS**

Even if there are no plans to specifically evaluate school cafeteria programs, it would be interesting to ask questions about children who benefit from them (namely those in primary school). We have therefore planned a minor module concerning the education of beneficiary children’s older siblings (attendance, grade level, assigned school). As school-aged children are expected to be in school during interviewers’ visits, the module will be posed directly to mothers.

### **3.2.6. Data analysis**

Statistical analyses will be performed using either R or STATA software. These analyses will take into account the characteristics of the sampling plan in strata (prefectures) and clusters (villages), and will be weighted according to village population sizes. The *p*-value, alpha, will be set at 0.05 and used as the threshold of significance for all comparisons.

Before the actual impact analysis, the results regarding indicators of interest will be presented by randomization group (intervention/beneficiary and control/non-beneficiary) at baseline in a descriptive fashion and by randomization group and prefecture at endline. Results concerning quantitative variables will be expressed in arithmetic mean values, while those dealing with qualitative variables will be expressed as frequencies (in percentages).

In order to evaluate program impact on the indicators of interest, the difference-in-differences method will be used. This method consists of comparing the intervention group to the control group both before and after the introduction of cash transfers. The underlying hypothesis is that absent the cash transfer program, the mean evolution of the indicators of interest should be the same in both groups. By considering an interaction term between the phase (baseline or endline) and the randomization group (intervention or control), this method permits evaluating whether the indicators’ evolution between the baseline and endline surveys differs significantly between the two groups. In other words, the difference-in-differences estimator compares the difference observed in the intervention group before and after program implementation with that observed in the control group. It also enables taking pre-existing differences between the intervention and control groups into account, as well as temporal effects, and thus allows for a conclusion on the existence of an impact attributable to cash transfers and/or the flexible conditionalities associated with them.

To this end, quantitative variable analysis will be conducted with the help of linear regression models, while qualitative binary variable analysis will be conducted with the help of logistic regression models. We will formulate
[figure not shown]

[figure not shown]
 (the estimation of the indicator of interest) and
[figure not shown]

[figure not shown]
 depending on whether we are interested in, respectively, a quantitative variable or a qualitative binary variable, in the following form:

**
[figure not shown]
=
[figure not shown]
+
[figure not shown]
*phase+
[figure not shown]
*group+
[figure not shown]
*phase*group**

Here, “phase” represents the survey (coded 0 for baseline and 1 for endline) and “group” represents the randomization group (coded 0 for the control group and 1 for the intervention group).
[figure not shown]
 is the effect of the phase (the difference between baseline and endline surveys),
[figure not shown]
 represents the difference between individuals in the intervention group and the control group, and
[figure not shown]
 represents the intervention’s effect on the intervention group or the difference-in-differences estimator.

**Using birthweight as an example, the table and figure below illustrate the significance of the various coefficients described above:**

[figure not shown]

[figure not shown]

Initially, analyses will be carried out via intention-to-treat (ITT) analysis; mother-child pairs (“CME”) and households will be analyzed within their initial randomization group, whether or not they have actually received cash transfers. A later set of analyses will use per-protocol analysis (or treatment-on-the-treated [TOT]); only mother-child pairs who have actually received cash transfers will remain in the intervention group, and those pairs who have not will be excluded from further analyses.

Pre-specified outcomes to be analyzed are as follows:

Primary outcomes:

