## **3.2. Methodology**

### **3.2.1. Approach**

The framework for analyzing the program’s impact will be experimental: all villages in the study area (*n*=162) will be randomly assigned either to an intervention group or a control group. Over a period of 24 months, cross-sectional surveys of children aged six to 29 months and their mothers will be conducted in these villages; one survey will take place before the program begins (hereinafter referred to as “baseline”) and the second will be conducted at the program’s end (hereinafter referred to as “endline”). A difference-in-differences analysis will permit both to determine whether situational evolution between the baseline survey and the endline survey differs significantly between the intervention group and the control group, and to conclude what impact is attributable to cash transfers and/or the flexible conditions with which they are associated.

Rationale for selected impact evaluation design:

1. ***Repeated cross-sectional vs. longitudinal design*.** We propose to use a repeated cross-sectional survey design rather than a longitudinal design primarily because our previous experience has shown that usual delays in program roll-out and full implementation can have profound effects on the evaluation study cohort (e.g. children aging out of the “window of opportunity” for maximum nutritional impact of the intervention – see point 2 below), making the cohort unusable for assessing impact on age-sensitive outcomes such as child feeding practices or stunting. Additional constraints of longitudinal designs include the logistical complexity and related additional cost of tracking individual children over time, compared to sampling children of a given age in a repeated cross-sectional design. However, given that our team has extensive experience with both types of designs, we are open to discussions with UNICEF and the World Bank regarding alternative designs.

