### **3.2.3 Sample size**

Sample size estimates are calculated based on changes in different impact indicators; HAZ and stunting and are based on the following principles:

- Using tests that compare means and prevalence between the two groups;
- Taking into account the design effect since randomization is carried out at the village level rather than individually;
- Using a conservative approach which consists of ignoring the fact that randomization is stratified by district;

The following parameters are fixed:

- 〈risk at 0.05;
- power at 90% ;
- 162 villages to be randomized (81 per group);
- Missing/invalid data at 10%;
- An intra-village correlation coefficient (ICC) that varies from 0.02 to 0.15

Based on the sample size estimates, we propose a sample size of 802 children aged six to 23 months/group, at baseline. This sample size will allow us to detect a difference of

9 points in prevalence of stunting and 0.20 in mean HAZ. This sample size will be extended to 1,020 children aged six to 29 months/group at baseline.

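### Difference-in-differences is unbiased for HAZ here, but it is less precise than an endline comparison adjusted for the village baseline mean, which uses the same data

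*Protocol*

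**What the plan says.** Section 3.2.1 sets the design: 162 villages randomised to two groups, and repeated cross-sectional surveys in those villages 24 months apart. It names the analysis: "A difference-in-differences analysis will permit both to determine whether situational evolution between the baseline survey and the endline survey differs significantly" between the groups.

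Section 3.2.6 writes the model out. It has an intercept, phase, group and their product, where phase "represents the survey (coded 0 for baseline and 1 for endline" and the product term is the impact estimate. Linear regression is used for quantitative outcomes and logistic regression for binary ones. The rationale is that the method "It also enables taking pre-existing differences between the intervention and control groups into account, as well as temporal effects". The section also requires analyses to account for district strata and village clusters and to weight by village population. HAZ is the only primary outcome. No baseline-adjusted endline model is mentioned.

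Section 3.2.3 sizes the trial with tests comparing means and prevalence between the two groups, at 90% power. Its inputs are "162 villages to be randomized (81 per group"), a 10% loss, and "An intra-village correlation coefficient (ICC) that varies from 0.02 to 0.15". The result is 802 children per group aged 6 to 23 months, to detect "9 points in prevalence of stunting and 0.20 in mean HAZ", extended to 1,020 per group aged 6 to 29 months. Both numbers are given for the baseline survey.

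**The concern.** The two reasons given for difference-in-differences are already met by the design. Randomisation removes systematic differences between groups in expectation, and the concurrent control group removes time effects. The baseline survey is therefore not needed for validity, and its remaining use is precision.

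The model keeps a group main effect next to the interaction, so it subtracts the whole observed baseline difference. Because the two surveys measure different children, only the village effect carries over between them. A mean of 9 to 11 children contains a good deal of sampling noise, and full subtraction passes that noise into the primary estimate. Regression adjustment gives the baseline mean only the weight its correlation with endline supports.

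At stake is the width of the interval for HAZ, and whether the power stated in section 3.2.3 applies to the analysis that will be run.

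**Working it through.** **Inputs from the protocol.** 81 villages per group; 802 or 1,020 children per group; 10% missing; ICC 0.02–0.15; difference 0.20 HAZ; alpha 0.05 (two-sided assumed).

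**Inputs assumed, because the protocol does not give them.** HAZ SD 1.0, with 1.3 as the unfavourable case. Correlation of true village effects between surveys (CAC) 0.8–1.0, with 0.5 as a check. Equal sample sizes at both surveys. Equal village sizes, with the planned population weighting ignored.

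**The plan's own figure.** Ignoring clustering, n per group = 2(1.96+1.282)²/0.20² = 525.4, so 526 at SD 1.0. Analysable children per village: 802×0.9/81 = 8.91. At ICC 0.047 the design effect is 1+7.91×0.047 = 1.372, and 526×1.372/0.9 = 802. So 802 fits a single-survey two-group comparison. This is not a strict reproduction, since the SD and the chosen ICC are not stated. For 802 to give difference-in-differences (DiD) 90% power, the SD would have to be about 0.78–0.90.

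**Formulas.** With m analysable children per village:

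- design effect: DE = 1+(m−1)×ICC
- correlation of village means: r = CAC×m×ICC/DE
- variance of the endline-only comparison: V = 2×SD²×DE/(0.9N)
- DiD variance: 2(1−r)V
- baseline-adjusted variance: (1−r²)V
- ratio of the last two: 2(1−r)/(1−r²) = 2/(1+r)
- power: Φ(0.20/SE − 1.96)

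The ratio exceeds 1 for every r below 1. The ranking of the two analyses therefore does not depend on SD, ICC or CAC; only the size of the loss does.

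**One case in full.** N = 1,020, SD 1.0, ICC 0.05, CAC 0.8.

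- m = 1,020×0.9/81 = 11.33; DE = 1+10.33×0.05 = 1.517; r = 0.8×11.33×0.05/1.517 = 0.299.
- Endline-only SE = √(2×1.517/918) = 0.0575.
- DiD SE = 0.0575×√1.402 = 0.0681; power = Φ(0.977) = 84%.
- Adjusted SE = 0.0575×√0.911 = 0.0549; power = Φ(1.685) = 95%.

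**Across the ICC range, SD 1.0.** Each cell runs from CAC 0.8 to CAC 1.0.

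| N per group | ICC | r | DiD variance / adjusted variance | DiD power | Adjusted power |
|---|---|---|---|---|---|
| 1,020 | 0.02 | 0.15–0.19 | 1.74–1.68 | 85–86% | 98% |
| 1,020 | 0.05 | 0.30–0.37 | 1.54–1.46 | 84–87% | 95–96% |
| 1,020 | 0.10 | 0.45–0.56 | 1.38–1.28 | 81–89% | 92–95% |
| 1,020 | 0.15 | 0.53–0.67 | 1.30–1.20 | 79–91% | 89–95% |
| 802 | 0.02 | 0.12–0.15 | 1.78–1.73 | 76–77% | 94–95% |
| 802 | 0.05 | 0.26–0.32 | 1.59–1.52 | 75–79% | 91–92% |
| 802 | 0.10 | 0.40–0.50 | 1.43–1.34 | 73–81% | 87–91% |
| 802 | 0.15 | 0.49–0.61 | 1.34–1.24 | 72–83% | 84–90% |

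**SD 1.3, same ICC and CAC ranges.** With 1,020 per group, DiD 57.0–71.5% and adjusted 68.4–86.3%. With 802 per group, DiD 49.8–61.1% and adjusted 62.0–78.5%.

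**Lower CAC.** At 0.5 with ICC 0.05 and SD 1.0, power is 70% against 90% (802) and 78% against 94% (1,020). The gap widens.

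**Simulation check.** Simulated means of 162 villages (9 children per village, SD 1.0, CAC 0.8, 3,000 runs per setting) gave these powers for endline-only, DiD and adjusted: 94/76/94% at ICC 0.02, 91/73/92% at ICC 0.045 and 74/71/83% at ICC 0.15. These agree with the formulas.

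**The case against.** The strongest reply is that nothing in section 3.2.6 is wrong. The quoted rationale is true, and difference-in-differences is a valid, pre-specified estimator. That stands: this is a matter of efficiency, and a reader who inferred bias would go further than the protocol supports.

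Several other points also stand and limit the claim:

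- **Power depends on unstated inputs.** It is tempting to say that adjustment restores the planned 90%. The protocol gives no SD and only a range for the ICC. With 802 per group and SD 1.0 the adjusted analysis falls to 84% at ICC 0.15, and at SD 1.3 it is below 90% throughout.
- **The correlation is inferred.** When r exceeds 0.5, at the top of the ICC range, difference-in-differences beats ignoring the baseline (83% against 73% with 802 per group, ICC 0.15, CAC 1.0). It still loses to adjustment, which gives 90% there.
- **Covariates.** The displayed equation has no district, age or sex term, but section 3.2.6 already requires strata and clusters to be accounted for, and a covariate list normally belongs in the SAP. No omission can be claimed.
- **Control villages.** Section 3.2.1 says all 162 villages are randomly assigned. Section 3.2.2 says 81 controls were selected from the remaining 192 without saying how. Anyone who doubts that step has a reason to want full differencing, so that analysis should be kept.
- **Binary outcomes.** The calculation covers a continuous outcome only and says nothing about the logistic models.

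**Conclusion.** The point holds as an inexpensive gain in precision for the primary outcome. With equal survey sizes, the planned analysis has 1.20–1.78 times the variance of the baseline-adjusted endline comparison over ICC 0.02–0.15 and assumed CAC 0.8–1.0. With 1,020 per group and assumed SD 1.0, that is roughly 79–91% power against 89–98%; with 802 per group, roughly 72–83% against 84–95%. The direction is certain under this model. The size rests on the assumed SD, CAC and equal survey sizes; unequal village sizes and the planned weighting would lower all these powers.

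The 90% in section 3.2.3 does not appear to be a difference-in-differences figure. That section speaks of changes in indicators, but it lists neither a baseline variance nor a between-survey correlation. A reader might go on to conclude that the sample size is wrong. The documents do not support that, because the SD and ICC behind 802 are not given.

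**What to change.** Before endline data are seen, specify the primary intention-to-treat analysis of HAZ as a regression of endline HAZ on group, adjusted for the village mean HAZ at baseline, with the strata and village clustering section 3.2.6 already requires. Compute that baseline mean in the same age range as the endline sample, and state the range: section 3.2.1 gives 6–29 months for the surveys, while section 3.2.2 gives 6–59 months at baseline and 6–30 months at endline. Keep the current phase-by-group model as a sensitivity analysis. Do not promise 90% power on the strength of the change, and do not carry it over to binary outcomes without a separate check.

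The cost is one paragraph of wording, no new data, and one degree of freedom out of about 160. The downside is that a chance baseline imbalance is only partly removed in the primary analysis; the retained difference-in-differences analysis covers this.

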2. ***Age range of children included in evaluation samples.*** The assessment of the impact of nutritional interventions on child anthropometry (as well as other outcomes) should consider the age at which assessments should be made to detect the greatest difference between intervention and comparison areas. Evidence suggests that (1) the *longer* children are exposed to early nutrition inputs (within the first 1,000 days, or from conception to the child’s second birthday) and (2) the *earlier* they are exposed within this period, the greater the impact will be.

Furthermore, achieved height-for-age is likely to be greatest between intervention and control children in the age period *after* the peak age of growth faltering (i.e., after 18-24 months of age).

The logic behind investments made from conception until the child’s second birthday is that they are progressive and cumulative; hence our ability to detect a significant impact on anthropometry particularly, will be greatest among those children who were exposed to interventions in the entire period preceding the peak age of growth faltering. This means that the age at which impact on anthropometry should be assessed is dependent on (1) the child’s age at the onset of their exposure to program interventions, (2) the total duration of exposure to interventions within the 9 to 24 month target age-focus, and (3) the peak age of growth faltering.

As impact on intermediary outcomes such as complementary feeding indicators will also be measured, we have to make sure that the corresponding age group (i.e. children > 6 months of age) is well represented in our sample.

We are applying these principles to define the exact age group for whom to assess impact on feeding and nutritional outcomes, taking into account demographic and logistical considerations.

1. ***Duration between baseline and endline surveys*.** Although the proposed pilot program will last 30 months, the need to ensure that baseline and endline assessments are conducted at the same time of the year (and thus minimize the impact seasonality has on key indicators of interest) means the duration between baseline and endline assessments should be 24 months apart (allowing extra time for preparation and post-survey analysis).

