**iii) describe the analysis’s context and take into account potential confounding factors**

- Village characteristics (facilities, equipment, etc.)
- Household demographics and socioeconomic characteristics
- Jobs and education levels of heads of households and women
- Hygiene
- Economic shocks endured by households

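### The impact model carries no individual covariates, so HAZ and other continuous child outcomes are estimated somewhat less precisely than the data already collected would allow

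*Protocol*

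**What the plan says.** Section 3.2.6 (Data analysis) states that "quantitative variable analysis will be conducted with the help of linear regression models" and assigns logistic regression to binary variables. It gives one equation for both: intercept, phase, group, and phase times group. Phase is "coded 0 for baseline and 1 for endline", group is the randomised arm, and the product term "represents the intervention’s effect on the intervention group or the difference-in-differences estimator". District strata, village clusters and population weights are accounted for. No individual-level covariate appears. HAZ is the only primary outcome.

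Other sections bear on what could have been included:

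- Section 3.2.5 says of mothers that their "height and weight will be measured in accordance with WHO recommendations". It also calls the mother's nutritional status a major factor in that of the newborn.
- Section 3.2.5 expresses children's measurements as z-scores on the WHO 2006 reference, which needs each child's age and sex.
- Section 3.2.1, point 2, builds the choice of age range around growth faltering. It expects the contrast between arms to be largest after "the peak age of growth faltering (i.e., after 18-24 months of age".
- Section 3.2.1, item iii, says data are gathered to "take into account potential confounding factors". Its list covers village, household, job, education, hygiene and shock variables, and none of the three discussed here.
- The one stated adjustment, for education and socioeconomic level, concerns mothers' knowledge, attitudes and practices (Section 3.2.5), not HAZ.

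**The concern.** In a linear model, whatever a prognostic variable explains stays in the residual if the variable is left out, and the standard error of the effect is larger for it. Each survey draws new children, so the four phase-by-arm cells will differ by chance in age, sex and maternal height. A model without these variables treats that variation as noise.

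HAZ is already standardised for age and sex, but only against the WHO reference. Growth faltering is a departure from that reference, and the sample spans the ages at which the protocol expects it. Age is therefore likely to remain prognostic for HAZ.

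At stake is the width of the interval for the primary outcome, and the chance of detecting the 0.20 HAZ difference named in Section 3.2.3.

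**Working it through.** **Inputs from the protocol (Section 3.2.3).** 81 villages per arm; 1,020 children aged 6-29 months per arm; 10% missing; ICC 0.02-0.15; alpha 0.05 (taken as two-sided); target difference 0.20 HAZ; power 90%.

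**The plan's own figure.** The 802 children per arm cannot be reproduced uniquely, because no HAZ SD is stated. With n0 = 2(1.96 + 1.2816)² SD² / 0.20² (rounded up), n = n0(1 − ICC) / (1 − n0·ICC/81), then division by 0.9:

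- SD 1.0, ICC 0.05: n0 = 526, result 823.
- SD 1.05, ICC 0.03: n0 = 580, result 797.
- SD 1.1, ICC 0.02: n0 = 636, result 822.

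So 802 is compatible with the stated inputs, and this point does not depend on it.

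**Assumptions not in the protocol.** HAZ SD 1.2; correlation of village means between surveys 0.5; share of within-village variance explained (R²) 8-18%.

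*Where the R² range comes from.* Suppose HAZ falls linearly by d between 6 and 24 months and is then flat, with ages uniform over 6-30 months. The variance due to age is then 0.109 × d²: 0.070, 0.109 and 0.157 for d = 0.8, 1.0 and 1.2. That is 5-16% of SD² for SD 1.0-1.2. Assumed contributions of 4-6% for maternal height and about 1% for sex bring the sum to 10-23%. The 8-18% used here is somewhat lower.

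**Formula.** Analysable children per village per survey: m = 1,020 × 0.9 / 81 = 11.33.

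Var(phase × group) = (4/81) × [ICC·SD²·(1 − 0.5) + (1 − ICC)·SD²·(1 − R²)/m]

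Power = Φ(0.20/SE − 1.96)

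**ICC 0.05.** The village part is 0.05 × 1.44 × 0.5 = 0.036. The within-village part is 0.95 × 1.44 / 11.33 = 0.1207.

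- R² = 0: (4/81) × 0.1567 = 0.00774, SE 0.0880, power 62.3%.
- R² = 8%: (4/81) × (0.036 + 0.1110) = 0.00726, SE 0.0852, power 65.1%.
- R² = 18%: (4/81) × (0.036 + 0.0990) = 0.00667, SE 0.0816, power 68.8%.

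**Across the protocol's ICC range (SD 1.2):**

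| ICC | SE, R² 0 | SE, R² 8% | SE, R² 18% | SE reduction | Power, R² 0 → 8% → 18% |
|---|---|---|---|---|---|
| 0.02 | 0.0828 | 0.0798 | 0.0759 | 3.7-8.4% | 67.5 → 70.8 → 75.1% |
| 0.05 | 0.0880 | 0.0852 | 0.0816 | 3.1-7.2% | 62.3 → 65.1 → 68.8% |
| 0.15 | 0.1033 | 0.1012 | 0.0985 | 2.0-4.6% | 49.1 → 50.7 → 52.8% |

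The percentage reduction in SE does not depend on SD; the power figures do.

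**Cross-check under other assumptions.** With SD 1.1, ICC 0.05, no correlation between surveys and R² 10%, difference-in-differences power moves from 60.9% to 63.7% if only within-village variance is explained, or to 65.5% if village-level variance falls in proportion. The size is similar.

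**The case against.** **A covariate list usually belongs in the analysis plan.** The equation can be read as introducing the estimator, and nothing in the protocol forbids adjustment. Item iii of Section 3.2.1 even foresees it. This has some force. But Section 3.2.6 does not leave the model open: it writes out every term and applies the form to the primary outcome, and item iii does not name the three variables. The point therefore concerns stated text.

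**There is no error to correct.** This stands. A reader might infer that leaving age out biases the effect, particularly since Section 3.2.2 gives ages 6-59 months at baseline and 6-30 at endline. The documents do not support that. Villages are randomised, the phase term absorbs an age shift common to both arms, and chance imbalance is sampling variation that the standard error already covers.

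**The argument fails for logistic models.** This also stands. A reader might extend the gain to stunting, wasting and binary feeding indicators. Adding prognostic covariates to a logistic model generally enlarges the standard error of the log odds ratio, and it changes the quantity estimated to a conditional odds ratio.

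**The size is assumed, and the prognostic case is partly inferred.** Correct. Section 3.2.1 implies rather than states that HAZ falls with age, and nothing says that sex predicts HAZ. At the top of the ICC range the gain is small. The low starting power comes from the variance of the difference-in-differences estimator, not from the missing covariates.

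**The covariates are not perfectly clean.** Birth registration is encouraged by the programme (Section 2.3.3), so recorded age could be more accurate in the intervention arm. A caretaker may replace a deceased mother (Section 2.3.1), leaving maternal height missing. Both are small and manageable.

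**Conclusion.** The point holds as a modest loss of efficiency for HAZ and other continuous child outcomes. It is not a flaw in validity. With R² 8-18% and a between-survey village correlation of 0.5, the standard error of the effect falls by about 2-8% over ICC 0.02-0.15. At SD 1.2, power for 0.20 HAZ rises by about 3 to 6 points at ICC 0.05, but by under 2 points at ICC 0.15 with R² 8%. The direction is secure provided the covariates are prognostic. The size rests on an SD, R² and correlation that the protocol does not give. The change would not by itself bring the difference-in-differences test to 90% power in any of the scenarios tabulated.

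**What to change.** In Section 3.2.6, prespecify the primary model for HAZ, WHZ and other continuous child outcomes as phase + group + phase × group + child age (spline or monthly bands) + child sex + maternal height. Keep the three-term model as a sensitivity analysis. For stunting, wasting and binary feeding indicators, if the same covariates are used, report standardised marginal differences, so that a conditional odds ratio is not set beside a crude one.

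Add two safeguards: age is ascertained by the same procedure in both arms and both surveys, and a rule is stated for missing maternal height where a caretaker has replaced the mother.

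The cost is a few lines of analysis text and, for binary outcomes, a standardisation step. Maternal height, age and sex are already collected or needed for the z-scores, so no extra child or measurement is required.
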